## Abstract

**Background:**

Allergic rhinitis (AR) is a common disease, and conventional medications are often insufficient for treatment. Bojungikgi-tang (BJIGT) is an herbal medicine widely used in traditional medicine and has anti-inflammatory and immunoregulatory effects. We hypothesize that BJIGT would improve nasal symptoms in patients with persistent AR (PAR).

**Methods:**

This is a randomized, double-blind, placebo-controlled, phase II trial. A total of 105 patients, identified with perennial allergens, with a history of PAR and a mean total nasal symptom score (TNSS) ≥ 5 during the run-in period will be recruited from Daejeon Korean Medicine Hospital. Participants will be randomly assigned to a high-dose BJIGT group, standard-dose BJIGT group, or control group (placebo) in a 1 : 1 : 1 allocation ratio after a week run-in period. The treatment medication will be taken three times per day for 4 weeks. The primary outcome measure is the mean change in the TNSS before and after medication. The secondary outcome measures include the Korean Allergic Rhinitis-Specific Quality of Life Questionnaire, total IgE and eosinophil count, overall assessment of AR, pattern identification questionnaire for AR, and Sasang constitution. *Discussion*. The aim of this study is to investigate the efficacy and safety of BJIGT in the treatment of PAR and to determine the suitable dosage of BJIGT. Therefore, we planned a randomized, controlled, phase II trial of two different doses of BJIGT compared with placebo, and the results of this study are expected to provide evidence for the use of BJIGT as a treatment of PAR. Trial Registration. The National Clinical Trial Registry Clinical Research Information Service, CRIS, KCT0006616, https://cris.nih.go.kr/cris/search/detailSearch.do/20706.

## 1. Introduction

Allergic rhinitis (AR) is an inflammatory disease of the nasal membranes by an immunoglobulin E (IgE)-mediated response that is characterized by rhinorrhea, nasal congestion, sneezing, and nasal itching as major symptoms [1]. AR can be categorized as intermittent AR (IAR) and persistent AR (PAR) based on symptom duration. AR is a common disease with a prevalence of 10% to 40% of the global population, and it has been increasing over the last decade [2]. Moreover, it is often accompanied by eye itching, tears, postnasal drip, and fatigue, and repeated AR can be a risk factor for comorbidities such as asthma, rhinosinusitis, and nasal polyps [3]. Although AR is not a threat to life, it has a considerable impact on daily and social activities [4], eventually generating substantial medical expenses and economic burden on the public health system.

The treatment of AR typically includes allergen avoidance, pharmacotherapy, immunotherapy, and patient education [5]. It is generally centered on medication for regulating allergic inflammation and relieving symptoms because it is difficult to avoid the causes of allergens, such as pollen, spores, dust mites, and animals in daily life. Oral and topical antihistamines, intranasal corticosteroids, decongestants, intranasal cromolyn, intranasal anticholinergics, and leukotriene receptor antagonists, either alone or in combination, are used for the symptomatic treatment of AR, depending on the individual patient's situation [6]. Oral antihistamines are more effective for neutrally mediated symptoms such as itching, sneezing, and rhinorrhea, whereas intranasal corticosteroids reduce nasal congestion more noticeably in moderate-to-severe rhinitis [7, 8]. For AR that cannot be controlled using the abovementioned medications, oral corticosteroids can be used for a short period, but not as high-dose steroid injections. Topical decongestants are only recommended for short periods of within a week to prevent adverse effects, such as atrophic rhinitis [9]. Depending on the recent Allergic Rhinitis and its Impact on Asthma Guidelines, intranasal corticosteroids and intranasal H1-antihistamine are recommended for PAR patients. However, all recommendations are conditional, and treatment may depend on preference for symptom reduction vs. the avoidance of adverse effects [2]. The potential adverse effects of each treatment depend on the class of drug. For example, intranasal corticosteroids may cause headache, throat irritation, and burning; high-dose antihistamines may cause sedation; and intranasal cromolyn may cause epistaxis and sneezing [10]. Although these side effects do not affect all patients, they may become more evident with long-term use, and some patients stop taking the medication because of it. Moreover, when the medication is stopped, the effects do not last [11].

Complementary medicine has been broadly used for the treatment of AR [12], and especially in Asian countries, many trials have evaluated the efficacy of several herbal medicines [13, 14], acupuncture [15], and so on. Bojungikgi-tang (BJIGT), also known as Bu-Zhong-Yi-Qi-Tang or Hochu-ekki-to, is an herbal medication that has been widely used in traditional medicine from old times. JIGT means that “tonify the middle and augment qi,” implying strengthening the digestive system and the immune system against many kinds of infections [16] and treating debilitating conditions resulting from chronic diseases [17]. Because of these effects, BJIGT is clinically used for various diseases such as atopic dermatitis, cancer-related fatigue, and anorexia. We paid attention to the anti-inflammatory and immunoregulatory effects of BJIGT for allergic diseases. According to previous studies, in preclinical trials, BJIGT showed inhibitory effects on the increase in the number of eosinophils and protective effects of nasal mucosal tissue in the AR [18] and immune-modulatory effects including downregulating Th2 responses, decreasing IgE, eotaxin, and eosinophils in the allergic asthma model [19]. These effects may be related to the reduction in allergic symptoms. In clinical trials, the nasal symptomatic scores were significantly improved in the BJIGT treatment group and BJIGT suppressed IgE, PGE2, LTC4, and COX-2 mRNA expression in IL-4-stimulated PMN in patients with PAR [20, 21]. Several survey studies have demonstrated that BJIGT was the second most clinically used national health insurance herbal medicine for AR or PAR in Korea [22, 23]. In addition, the safety of BJIGT has been proved in the trial of 13-week oral repeated-dose toxicity [24]. However, no randomized controlled trial has evaluated BJIGT compared with placebo in the treatment of AR in Korea.

We hypothesize that BJIGT would improve nasal symptoms in patients with PAR. The aim of this study is to investigate the efficacy and safety of BJIGT in the treatment of PAR and to determine the suitable dosage of BJIGT. Therefore, we planned a randomized, double-blind, placebo-controlled, phase II trial of two different doses of BJIGT in comparison with placebo.

## 2. Methods/Design

### 2.1. Study Design

This study is a randomized, double-blind, placebo-controlled, phase II trial to evaluate the efficacy and safety of BJIGT for PAR. The trial will be conducted at the Daejeon University Daejeon Korean Medicine Hospital in Korea. We followed the methods of Lee et al. [25].

A total of 105 participants will be recruited for this trial and randomly assigned to a high-dose BJIGT group, standard-dose BJIGT group, or control group (placebo) in a 1 : 1 : 1 allocation ratio. The trial will consist of a 1-week run-in period after screening and a 4-week treatment period. Participants will take medications three times a day for 4 weeks, with visits at 2-week intervals; the detailed study design is summarized in Figure 1 and Table 1.

### 2.2. Participants

#### 2.2.1. Inclusion/Exclusion Criteria

The inclusion criteria are as follows: (1) age 19–65 years; (2) PAR (symptoms > 4 days/week and >4 consecutive weeks) with a history of at least 2 years prior to study participation; (3) positive reactions to perennial allergens in allergy skin tests (e.g., skin prick test or intradermal test), multiple allergen simultaneous test (MAST), or Immuno CAP that were conducted within 12 months. The criteria for positive responses to specific allergens are defined as follows—prick tests: a wheal size of ≥3 mm compared with the diluent control; intradermal tests: a wheal size of ≥7 mm compared with the diluent control; MAST or Immuno CAP: ≥ class 2; (4) average daily reflective total nasal symptom score (r-TNSS) of ≥5 at the third visit during the run-in period; (5) the ability and willingness to record subject diaries; (6) equally maintain the surrounding environment during the entire period of the clinical study; and (7) voluntarily agreed to participate in this clinical study in written form.

The exclusion criteria are as follows: (1) nonallergic (angioneurotic, infectious, and drug-induced) rhinitis; (2) presence of asthma; (3) clinically significant nasal deformities, such as obstructive nasal polyps or nasal septum; (4) experienced damages around the nasal cavity or surgeries within 12 weeks; (5) a past medical history of acute or chronic sinusitis within 4 weeks; (6) initiated immunotherapy or changes in dosage within 4 weeks; (7) experienced use of long-acting antihistamines; (8) upper respiratory tract infections, including the common cold, and systemic infections within 2 weeks; (9) comorbidities or clinical significant disorders of the kidney, liver, psychiatric system, cardiovascular system, respiratory system, endocrine system, and central nervous system, which may interrupt the treatment of cancers, the safety assessment, or completion of this clinical study; (10) abnormal renal function (creatinine values ≥ 2 times the upper limit of normal); (11) severe abnormal liver function tests (alanine transaminase (ALT) or aspartate transaminase (AST) values ≥ 2 times the upper limit of normal); (12) hepatitis A (active), hepatitis B (active), or hepatitis C; (13) unregulated hypertension (systolic blood pressure > 180 mmHg or diastolic blood pressure > 100 mmHg); (14) electrolyte abnormalities (potassium test readings outside the normal range); (15) hypokalemia, administering drugs (such as furosemide, thiazide, amphotericin, cisplatin, and digitalis), or a condition that can show hypokalemia (such as hypomagnesemia, Bartter syndrome, and Gitelman syndrome); (16) anticoagulants (heparin, warfarin, aspirin, etc.) for cardiovascular disorders or blood coagulation disorders; (17) blood coagulation abnormalities (PT-INR and aPTT readings outside the normal range); (18) the use of concomitant medications or those who are expected to require the use of prohibited concomitant medications during the period of the clinical study a minimal period following the use of concomitant medications has passed (3 days for nasal passages, topical, eye drops, or systemic antihistamines (10 days for long-acting agents, such as loratadine, fexofenadine, and cetirizine; 14 days for ketotifen; and 3 months for astemizole); 14 days for cromolyn nasal or nedocromil; 3 days for anticholinergics; 3 days for nasal or systemic decongestants; 30 days for nasal or systemic corticosteroids; 3 days for reserpine; 3 days for antitussives and expectorants; 7 days for leukotriene modifiers; 14 days for systemic antibiotics; 2 days for nonsteroidal anti-inflammatory drugs (NSAIDs) (a low-dose aspirin below 100 mg can be used); and 14 days for traditional herbal medicinal products that may affect rhinitis and eye symptoms); (19) chronically used tricycle antidepressants, beta-agonists, and bronchodilators that may affect the efficacy of test drugs; (20) r-TNSS during the baseline period within 1 week of the third visit was recorded for less than 4 days; (21) plan of long-term movement to other areas during the period of the clinical study; (22) history of excessive alcohol use or drug addiction; (23) history of hypersensitivity reaction to active ingredients or excipients of the investigational product; (24) genetic disorders, such as galactose intolerance, Lapp lactase deficiency, or glucose-galactose malabsorption; (25) subjects who did not agree to use contraception by medically permitted methods (e.g., surgical treatment of infertility, intrauterine device, condom or diaphragm, and injectable or insertable contraceptives) during the period from dosing of the investigational drug to 90 days after the clinical study among female subjects of childbearing potential and male subjects with a female partner; (26) pregnant or lactating women; (27) participation in a different clinical study within 4 weeks before participation in this trial; and (28) subjects who were determined to be ineligible to participate in this trial.

To determine whether the rhinitis is allergic, potential participants will be examined using MAST at the screening, and participants classified as class 2 or higher in the MAST that tests 108 types of allergens will be enrolled. Each patient's enrollment will be determined by the investigator, a Korean medicine doctor who treats allergies and respiratory diseases. During the trial period, the participant can voluntarily withdraw at any time or can be dropped at the discretion of the researcher.

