### 2.3. Interventions

The participants will receive placebo for a 1-week run-in period and high-dose BJIGT or standard-dose BJIGT or placebo for the 4-week treatment period. BJIGT and placebo granules are sealed in aluminum bags, and the participants will be instructed to take two packets of medicine (5.0 g) with water three times per day after each meal. The dosage is determined to be 15 g per day for the high-dose BJIGT and 7.5 g per day for the standard-dose BJIGT according to the Korean Ministry of Food and Drug Safety (MFDS) approval and the pharmacologically active dose in expectorant effective tests [29].

The BJIGT to be used in this study is composed of dried brown granules, and the extract is allowed and controlled by the Korean MFDS. Hankookshinyak Corporation (Nonsan, Korea) manufactures the BJIGT and placebo in accordance with Korea Good Manufacturing Practice standards. A 2.5 g sample of BJIGT consists of ten medicinal herbs: Ginseng Radix 0.665 g, Atractylodis Rhizoma 0.665 g, Astragali Radix 0.665 g, Angelicae Gigantis Radix (0.5 g), Citri Unshius Pericarpium 0.335 g, Bupleuri Radix 0.335 g, Zizyphi Fructus 0.335 g, Glycyrrhizae Radix 0.25 g, Cimicifugae Rhizoma 0.165 g, and Zingiberis Rhizoma 0.085 g. The placebo does not include any of these active ingredients and is made of lactose, corn starch, caramel coloring, etc. Both granules had the same shape, weight, and color as gray brown.

The participants will record their symptoms twice daily—morning and evening—in their TNSS diary for a total of 5 weeks. To improve and evaluate compliance, participants will be requested to record their dosage and return the remaining medications at the third, fourth, and fifth visits. Additional therapeutic interventions for AR equivalent to the exclusion criteria of the protocol will not be permitted during the trial.

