#### 2.4.2. Secondary Outcome Measures

*KARQLQ*. Measurement of AR-specific quality of life (QOL) impairment is significant for the assessment of the burden and efficacy of treatment. We will use the Korean Allergic Rhinitis-Specific Quality of Life Questionnaire (KARQLQ), which is the validated QOL questionnaire for Korean AR patients that consists of 15 questions about activities, nasal symptoms, practical problems, and other symptoms with a 5-point scale [31]. The KARQLQ will be measured at the third, fourth, and fifth visits (weeks 0, 2, and 4).

*Total IgE and Eosinophil Count*. Total IgE and eosinophil counts will be examined at the third and fifth visits (weeks 0 and 4) to assess the impacts of BJIGT on allergic and inflammatory responses. BJIGT has been demonstrated to have antiallergic and anti-inflammatory effects in animal studies and several clinical studies [18, 21].

*Overall Assessment of Allergic Rhinitis*. The overall degree of symptom changes for AR will be evaluated after treatment (fifth visit, week 4). The following scoring method will be used: 0 = very much improved, 1 = much improved, 2 = slightly improved, 3 = no change, 4 = slightly worse, 5 = much worse, and 6 = very much worse [32].

*Pattern Identification Questionnaire for AR*. To seek a more precise use of BJIGT, we will use the pattern identification (PI) questionnaire for AR based on a traditional Korean medicine perspective. The PI questionnaire for AR V.3.0 was developed by specialists in the Department of Otolaryngology of Korean medicine [33]. This questionnaire sorts patients with AR as possessing lung-heat, lung-cold, or spleen qi deficiency using the nasal symptoms and general conditions of AR patients.

*Sasang Constitution*. The Sasang constitution system by constitutional typology in Korean medicine differentiates individuals into four constitutional types. We will use the revised questionnaire for the Sasang Constitution Classification (QSCC II+) to refer to the differences in the effects of the Sasang constitution [34].

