#### 2.4.3. Safety Assessment

Safety will be assessed through laboratory examinations, vital signs, and adverse events (AEs). To observe the safety of the participants, complete blood cell counts, blood coagulation test, blood chemistry examination (liver and kidney function test), serum hepatitis test, and urine test will be conducted at screening and at the fourth and fifth visits. The investigator will check vital signs and any unexpected or expected AEs at every visit and record details on a case report form (CRF). If serious AEs occur, the investigator will promptly stop the subject from taking medication and report it in accordance with the guidelines of the IRB.

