### 2.5. Assignment of Interventions

#### 2.5.1. Allocation

The randomized allocation sequence will be produced by an independent statistician using SAS version 9 statistical software (SAS Institute, Cary, NC). The subject who meets the criteria will be given an identification code (random assignment number) with the same allocation ratio of 1 : 1 : 1 for a high-dose BJIGT, standard-dose BJIGT, or placebo group. The statistician will keep the randomization table separately until the blinding of the trial is maintained. The assignment is planned according to the assignment table created by a random assignment method that can be specifically designed and reproduced in advance. The statistician manages the assignment table, and the file is kept closed-door.

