## Figures and Tables

**Figure 1 fig1:**
[figure not shown]
Flowchart of the study plan. BJIGT, Bojungikgi-tang.

**Table 1 tab1:** Schedule of enrollment, interventions, and outcome measurements.

Time point, wk	Screening	Run-in period	Study period		
	−2 W	−1 W	0 W	4 W	8 W
Visit	1	2	3	4	5
Enrollment					
Informed consent	X				
Eligibility screen	X	X			
Allocation			X		
Demographic characteristics	X				
Medical history	X				
Chest X-ray, EKG	X				
Vital signs	X	X	X	X	X

Interventions					
Prescription		X	X	X	
High-dose BJIGT					
Standard-dose BJIGT					
Placebo					

Assessments					
Clinical laboratory test^(1)^	X			X	X
Pregnancy diagnosis test	X				X
MAST	X				
TNSS					
KARQLQ			X	X	X
Biomarkers^(2)^			X		X
Overall assessment					X
Pattern identification			X		
Sasang constitution			X		
Compliance			X	X	X
Adverse reaction assessment		X	X	X	X

(1) complete blood cell count tests, blood coagulation test, blood chemistry examination (liver and kidney function test), serum hepatitis test, and urine analysis; (2) total IgE, eosinophil count. BJIGT, Bojungikgi-tang; MAST, multiple allergen simultaneous tests; TNSS, total nasal symptoms score; KARQLQ, Korean Allergic Rhinitis-Specific Quality of Life Questionnaire.

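### Contraception is required only from dosing, 1 to 2 weeks after the sole pre-treatment pregnancy test, and no test is scheduled at allocation

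*Protocol article*

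**What the plan says.** Three parts of the protocol article bear on this point.

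- **Contraception (Section 2.2.1, exclusion 25).** Women of childbearing potential, and men with a female partner, are excluded unless they agree to contraception "during the period from dosing of the investigational drug to 90 days after the clinical study". No other section sets an earlier start.
- **Pregnancy (Section 2.2.1, exclusion 26).** The criterion reads "pregnant or lactating women", with no time limit. Section 2.5.1 ties allocation to eligibility: "The subject who meets the criteria will be given an identification code".
- **Testing (Table 1).** The row "Pregnancy diagnosis test" is marked at visit 1 (screening, −2 W) and visit 5, and is blank at visits 2, 3 and 4. Allocation is marked at visit 3 (0 W).

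On dosing, Section 2.3 states "The participants will receive placebo for a 1-week run-in period". In Table 1 the run-in begins at visit 2 (−1 W). Randomised product follows from visit 3 for 4 weeks.

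**The concern.** The plan itself treats exposure in pregnancy as a risk: it excludes pregnant women and carries the contraception duty to 90 days after the study. For that protection to work before treatment, a negative test and the contraception duty have to meet. Either contraception runs from the test onward, or the test is repeated at the moment exposure begins. Here neither is done. The duty begins at dosing, the test precedes dosing by one or two weeks, and allocation has no test of its own.

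At stake is an unrecognised pregnancy, conceived between visit 1 and the start of the duty, in a participant who is then allocated to BJIGT. Unless she notices and reports it, the next scheduled test comes only at the end of treatment. Type I error, power and the TNSS comparison are unaffected.

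**Working it through.** There is no stated figure to reproduce. The check is one of timing, using the Table 1 week headings and the durations in the text.

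**Inputs**

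| Item | Value | Source |
|---|---|---|
| Visit 1, pregnancy test | −2 W | Table 1 |
| Visit 2, start of run-in placebo | −1 W | Table 1; Section 2.3 |
| Visit 3, allocation and first randomised dose | 0 W | Table 1; Section 2.3 |
| Treatment length | 4 weeks | Sections 2.1 and 2.3 |
| Visit 5, second pregnancy test | week 4 in the text, 8 W in the Table 1 heading | Section 2.4.2; Table 1 |

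**Is the table read correctly?** The laboratory row is marked at visits 1, 4 and 5. Section 2.4.3 says the same in words: "serum hepatitis test, and urine test will be conducted at screening and at the fourth and fifth visits". The columns therefore line up, and the pregnancy row can be trusted.

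**Does another scheduled test fill the gap?** No. Table 1 note 1 itemises the laboratory panel as blood count, coagulation, chemistry, hepatitis serology and urinalysis. Pregnancy is a separate row and is not marked at visit 4. The eligibility screen is marked again at visit 2, but without a pregnancy test.

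**Interval from the negative test to the start of the contraception duty**

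- If dosing means randomised product: 0 − (−2) = 2 weeks.
- If dosing includes run-in placebo: −1 − (−2) = 1 week.

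**Interval from the negative test to the first possible BJIGT dose:** 0 − (−2) = 2 weeks under either reading.

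**Interval between the two scheduled tests**

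- By the text: 2 weeks before allocation + 4 weeks of treatment = 6 weeks.
- By the Table 1 headings: 8 − (−2) = 10 weeks.

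The text is the better guide. Section 2.1 says "Participants will take medications three times a day for 4 weeks, with visits at 2-week intervals", which puts visit 5 at week 4. The disagreement in the later headings does not alter the interval before dosing.

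**Exposure before the visit 5 test:** up to the full 4 weeks of treatment.

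**Number concerned:** 105 × 2/3 = 70 participants are to be allocated to one of the two BJIGT arms. This is not a count at risk, since it includes men and women who cannot conceive. The article gives an age range of 19–65 but no number of women of childbearing potential, so no event probability can be derived.

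**The case against.** The strongest reply is that nothing here contradicts anything else. The plan tests at both ends, excludes pregnancy, requires contraception during exposure and for 90 days afterwards, and was approved by the regulator and the ethics board. An earlier start could be called a preference. The article is also condensed: counselling, reporting of a suspected pregnancy and testing on suspicion may be in the full protocol or consent form, which are not shown.

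The last point is fair for unscheduled safeguards. It does not reach the gap itself, because the article fixes both the start of the duty and the visit-by-visit tests. A fuller document could remove the gap only by departing from them. Approval shows that the schedule was accepted, not that the two parts meet.

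Other points carry some weight:

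- **Existing contacts.** The repeat eligibility screen at visit 2 and the adverse reaction checks at visits 2 to 4 are occasions on which a pregnancy could be raised. None includes a test.
- **The 2-week lead.** It rests on the Table 1 headings, whose later columns disagree with the text, while Section 2.1 mentions only a 1-week run-in after screening. However, the columns at −2, −1 and 0 are consistent with a 1-week run-in. Even if screening came immediately before the run-in, a 1-week gap would remain where dosing means randomised product. The gap would close only if the run-in placebo also counted as dosing.
- **Continuous methods.** Several permitted methods, such as sterilisation or an intrauterine device, work continuously. For women already using them the gap is largely nominal.
- **Limits of the remedies.** An earlier contraception start does not reveal a pregnancy too early to detect at visit 1, and a visit 3 test may miss a conception only days old. The two measures complement each other.

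**Conclusion.** The concern holds as a minor participant-safety point. As written, 2 weeks after the only pre-treatment test carry no contraception duty, or 1 week if run-in placebo counts as dosing, and pregnancy status is not tested again before active treatment. The consequence is possible exposure of an unrecognised pregnancy for up to 4 weeks.

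This rests on the Table 1 timing of visits 1 to 3 and on the absence of any unscheduled safeguard described in the article. The likelihood of the event cannot be estimated from the document and may well be small, given the short interval and the probable existing use of contraception by many participants. The change is worth making because it is cheap, not because the risk is shown to be large.

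**What to change.** **Main change.** Reword exclusion (25), and the consent form to match, so that the contraception agreement runs from consent/screening at visit 1 until 90 days after the study. This closes the interval whichever way dosing is understood. The cost is a change of wording and a commitment longer by at most 2 weeks.

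**Optional addition.** Mark a pregnancy test in Table 1 at visit 3, with the result known before the first randomised dose. This is the step that could detect a pregnancy before exposure and would give exclusion (26) support at allocation. It costs one test per woman of childbearing potential and needs no extra visit, since sampling already takes place then: "Total IgE and eosinophil counts will be examined at the third and fifth visits".
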